## Measurements

### Fluids intakes (IV, ORS, and water)

ORS will be given to the after measuring with a calibrated cylinder and the amount intake will be recorded every 6 hours, in case of any leftover that will be deducted from previous order. Water intake will also be measured in a similar way. When needed IV fluid will be infused through a calibrated soluset, the amount infused will be recorded every 6 hours if the child requires IV fluid therapy.

### Output (stool, urine and vomitus)

Stool will be collected in a bucket of known weight beneath the cholera cot with a central hole and will be measured every 6 hours with an electronic scale of a precision of 1 gram. Urine will be collected by pediatric urine collector (PUC bag) and measured with a calibrated cylinder in ml. Vomitus will be collected in a pre-weighed bowl and measured with an electronic scale. The children will be offered a defined food of known calorie after measuring with an electronic scale of precision 1 g. Any leftover will be measured and subtracted from the amount offered and amount ingested will be recorded every 6 hours. Nude body weight will be measured at admission, after rehydration, and every 6 hours until recovery from diarrhoea and then at the end of every 24 hours and at discharge. Clinical evaluation will be performed every morning and evening. Resolution of diarrhea will be defined as the passage of two consecutive soft/formed stools or no stool for 24 hours. Therapeutic success will be defined as the cessation of diarrhea within 7 days of inclusion in the study treatment. Duration of diarrhea will be calculated in hours from the time of randomization to the last watery or loose stool within 7 days. Children will be considered withdrawn from the study if their parents or legal guardian withdraw consent, or the child is withdrawn from study for treatment of any complications; data (intakes and outputs) of such children up to the time of withdrawal will be included in the analysis (intent to treat analysis). Data of the children who failed to recover within seven days (study period) will also be included in the analysis for a maximum of seven days; those will be labelled as therapeutic failures and will be treated in the hospital until recovery.

Primary outcome measures will be; duration of diarrhea, proportion of patients recovered within 72 hours, and daily stool output.

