### **Statistical methods**

All data will be entered into microcomputer and analyzed using the software 'Statistical Package for Social Science'; version 20.0, Chicago, IL. Continuous variables will be compared between groups with student's t-test and nonparametric test. Categorical variables will be compared by chi-square test. Kaplan-Meier survival curves will be constructed for the duration of diarrhoea and for comparison with log rank test; a p value <0.05 will be considered as statistically significant. To see

whether there are significant differences among the groups, we will perform ANOVA to systematically examine variability within groups being compared.

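### Duration of diarrhea does not require observed resolution, so a child withdrawn while still purging scores a short duration and unequal early withdrawal biases the comparison

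*Protocol*

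**What the plan says.** All the rules on outcomes and withdrawals stand in one paragraph of the Protocol, under *Output (stool, urine and vomitus)*.

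- Resolution: "Resolution of diarrhea will be defined as the passage of two consecutive soft/formed stools or no stool for 24 hours".
- Duration: "Duration of diarrhea will be calculated in hours from the time of randomization to the last watery or loose stool within 7 days". Resolution is not a condition of this definition.
- Withdrawal: a child leaves the study if consent is withdrawn or if "the child is withdrawn from study for treatment of any complications". For these children, "data (intakes and outputs) of such children up to the time of withdrawal will be included in the analysis (intent to treat analysis".
- Day-7 non-recoverers: children who "failed to recover within seven days (study period) will also be included in the analysis for a maximum of seven days", and "those will be labelled as therapeutic failures and will be treated in the hospital until recovery".
- Outcomes: "Primary outcome measures will be; duration of diarrhea, proportion of patients recovered within 72 hours, and daily stool output".

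Under *Statistical methods*, Kaplan-Meier curves and a log-rank test are assigned to duration, with no statement of who is censored. The same section adds: "Continuous variables will be compared between groups with student's t-test and nonparametric test". ANOVA is also planned for differences among groups.

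The sample-size section rests on a 25% reduction in 48-hour stool output, 5% significance, 90% power and 10% drop-out, giving 46 per group.

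**The concern.** The last loose stool recorded marks the end of diarrhea only if the child was watched until diarrhea stopped. For a child withdrawn while still purging, it marks the end of observation. The duration definition does not separate the two cases. The withdrawal rule then brings the child in with whatever was recorded and calls this intention to treat. Day-7 non-recoverers are given a failure label, but withdrawn children are given no status: not failed, not censored, not unrecovered.

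Withdrawal for a complication is a poor outcome, yet under this rule it yields one of the shortest durations in the trial. If one arm has more such withdrawals, the first-listed primary outcome moves in that arm's favour. The Introduction itself notes that low-molecular-weight soluble fibres have been hypothesized to cause gastrointestinal symptoms, including osmotic diarrhea, so a difference between arms cannot be ruled out.

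**Working it through.** **1. Inputs.** From the Protocol: 46 per arm, 5% significance, a 7-day limit (7 × 24 = 168 h), and one overall 10% drop-out allowance. Not in the Protocol and therefore assumed: the distribution of duration, and the withdrawal rates and times by arm. The main scenario takes lognormal durations (median 72 h, log-SD 0.6), withdrawals spread evenly over 6–36 h, and no true treatment effect.

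**2. The plan's own figure.** No SD is given, so 46 can only be solved backwards. With n = 2(1.960 + 1.282)² × (CV/0.25)² and CV = 0.345, n = 21.01 × 1.904 = 40.02, rounded up to 41; 41/0.9 = 45.6, rounded up to 46. So 46 corresponds to an SD of about 34.5% of the control mean. The figure can be neither confirmed nor refuted, and nothing below depends on it.

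**3. Size of the bias by hand.** The expected duration capped at 168 h is 72·e^0.18 × Φ((ln(168/72) − 0.36)/0.6) + 168 × [1 − Φ(ln(168/72)/0.6)] = 86.2 × 0.792 + 168 × 0.079 ≈ 81.5 h. A withdrawn child is recorded at about (6 + 36)/2 = 21 h. With withdrawals of 10% vs 2%, the spurious difference is 0.08 × (81.5 − 21) ≈ 4.8 h. If 72-hour recovery were read off the truncated duration, half of the withdrawn children would be miscounted as recovered: 0.08 × 0.5 = 4 points.

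**4. Effect on the tests.** The table gives the rate of falsely concluding benefit in the arm with more withdrawals (nominal 2.5%), with no true effect. The Weibull rows assume median 72 h, shape 1.5, withdrawals over 0–48 h, a last stool about 4 h before withdrawal or day 7, and 1,500 runs.

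| Withdrawal by arm | Model | Mean difference | t-test | Log-rank, all durations as events | Log-rank, censored |
|---|---|---|---|---|---|
| 10% vs 2% | lognormal | −4.8 h | 7.2% | 6.3% | 2.7% |
| 10% vs 0% | Weibull | −5.8 h | 8.0% | 6.0% | 2.0% |
| 20% vs 0% | Weibull | −12.1 h | 20.6% | 14.2% | 2.3% |
| 30% vs 10% | Weibull | −12.0 h | 22.3% | 17.8% | 2.7% |
| 10% vs 10% | Weibull | +0.2 h | 2.8% | 3.1% | 2.8% |

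The first row agrees with the hand calculation. The censored column removes withdrawals at withdrawal and non-recoverers at 168 h. Withdrawal is unrelated to prognosis in these simulations, which is the favourable case for censoring.

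**5. Stool output.** Assume 100 g/kg/day at the start, with a half-life of 48 h (k = ln 2/48 per hour). Cumulative output is (100/24)(1 − e^(−kt))/k, which gives 84.5 g/kg at 24 h and 144.3 g/kg at 48 h. A child withdrawn at 24 h therefore contributes 84.5 instead of 144.3 to a 48-hour total. The mean per observed day moves the other way: 84.5 against 144.3/2 = 72.1, because the early days are heaviest.

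**6. Day-7 non-recoverers.** They receive about 164–168 h. With true medians of 72 vs 96 h and no withdrawals, coding them as completed gives a mean difference of −18.7 h where the true difference is −28.0 h, and log-rank power of 44.6% against 50.1% when they are censored. With the test arm truly worse (96 vs 72 h), false benefit was 0%.

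**The case against.** The strongest defence is that log-rank is assigned specifically to duration, and that including data up to withdrawal is how a censored child enters such an analysis. The withdrawal sentence speaks of intakes and outputs and does not assign a recovery event. Detailed censoring conventions are commonly left to a SAP, which may exist. The t-test sentence is generic and does not name duration. The 10% drop-out is a single overall allowance, and blinding together with the phase I tolerability step makes a large gap between arms less likely.

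Much of this stands. A reader might infer that the Kaplan-Meier curve will have nothing censored, but the Protocol does not say so; it simply gives no rule. What does not fall away is the endpoint definition. The Protocol itself fixes duration at the last loose stool and labels the withdrawal rule intention to treat, so a SAP that follows it literally inherits the bias.

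Three stronger readings are tempting and unsupported:

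- That all three primary outcomes are biased. A child withdrawn while purging does not meet the resolution criterion, so 72-hour recovery goes wrong only if it is derived from the truncated duration. Daily stool output averaged over observed days is not lowered; only a 48-hour or other cumulative total is.
- That day-7 failures add false benefit. They carry a failure label and near-maximal durations, so completed coding only compresses the difference.
- That the drop-out allowance shows unequal withdrawal. It says nothing about the separate arms.

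**Conclusion.** The point holds for duration of diarrhea. As written, the rule gives a child withdrawn before resolution a short completed duration, and any excess of early withdrawals biases the comparison towards that arm. The same follows for 72-hour recovery if it is taken from that duration, and for a 48-hour stool total, which is the measure used for sizing.

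Under the assumed 10% vs 2% withdrawal, the false-benefit rate is about 6–7% against a nominal 2.5%, and about 2.5% again with censoring. Larger gaps do more harm, and equal withdrawal does none. The duration distributions and the withdrawal rates and times are assumptions. The size changes with them, but the direction under the literal rule does not. Because this is a stated rule on a primary outcome that can score harm as benefit, it should be corrected before analysis.

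**What to change.** Under *Output (stool, urine and vomitus)*:

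- Count recovery as an event only when the stated resolution criterion is met.
- Censor withdrawn children at withdrawal and unrecovered children at 168 h.
- Count children withdrawn before resolution as not recovered at 72 h.
- Add a sensitivity analysis that keeps children withdrawn for complications as not recovered to 168 h, because censoring them may be informative.
- State how 48-hour stool output is computed when collection is incomplete, so that a partial collection is not treated as a complete total. A simple rate per observed hour would not serve, since it overstates output for early withdrawals.

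Under *Statistical methods*: name the log-rank test, with these censoring rules, as the test of duration in place of the t-test and ANOVA.

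The cost is protocol and analysis wording. Stool is already measured every 6 hours, so no new data are needed beyond recording the time of and reason for each withdrawal.

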**Outcome measures/variables:**

Main outcome measures will be; duration of diarrhoea, proportion of patients recovered within 72 hours, and daily stool output.

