### **Sample Size Calculation and Outcome (Primary and Secondary) Variable(s)**

Clearly mention your assumptions. List the power and precision desired. Describe the optimal conditions to attain the sample size. Justify the sample size that is deemed sufficient to achieve the specific aims.

Based on the results of a clinical trial of ORS solution in children with acute watery diarrhea with an anticipation of a 25% reduction in 48-hour stool output after in children after receiving Fibersol-2 dissolved with drinking water. Considering 5% level of significance and 90% power and 10% drop out the sample size is estimated to be 46 in each group [14]. However, for the tolerability and acceptability study we have selected 30+30=60 children suggested by the respected members of the RRC and ERC respectively.

For the tolerability and acceptability study in healthy Study group 1, 15 healthy children will receive Fibersol-2, 2.5 mg twice daily

Study group 2, 15 healthy children will receive Fibersol-2, 5mg twice daily

For the tolerability and acceptability study in children with diarrhea Study group 1, 15 diarrheal children will receive Fibersol-2, 2.5g twice daily

Study group 2, 15 diarrheal children will receive Fibersol-2, 5g twice daily

For RCT in diarrheal children:

Study group 1, 46 will receive Fibersol-2 dissolved in 50 ml drinking water, twice daily (suitable dose from the tolerability and acceptability trial)

Study group 2, 46 will placebo (regular maltodextrin) dissolved in 50 ml drinking water, twice daily (same dose as in Fibersol-2)

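### The trial is sized on 48-hour stool output, but three differently defined outcomes are declared primary with no success rule, so the stated 90% power and 5% error do not together describe the primary analysis

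*Protocol*

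**What the plan says.** The protocol's Measurements section, under Output (stool, urine and vomitus), states: "Primary outcome measures will be; duration of diarrhea, proportion of patients recovered within 72 hours, and daily stool output". The Project Summary lists the same three: "Main outcome measures will be; duration of diarrhoea, proportion of patients recovered within 72 hours, and daily stool output". Neither place ties daily stool output to a particular day or to a cumulative period.

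The section Sample Size Calculation and Outcome (Primary and Secondary) Variable(s) rests on the "anticipation of a 25% reduction in 48-hour stool output" and continues: "Considering 5% level of significance and 90% power and 10% drop out the sample size is estimated to be 46 in each group". It gives no control mean, standard deviation or sidedness. Despite its heading, it does not say which variables are primary and which secondary. It makes no power statement for duration or for 72-hour recovery.

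Statistical methods assigns a t-test and a nonparametric test to continuous variables and a chi-square test to categorical ones. For duration it says "Kaplan-Meier survival curves will be constructed for the duration of diarrhoea and for comparison with log rank test", followed by "a p value <0.05 will be considered as statistically significant". No other threshold, order of testing or adjustment is given, and nothing says whether one primary outcome or all of them must succeed.

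Specific Objectives states the efficacy aim as reducing the duration of watery diarrhea and stool output.

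**The concern.** A power statement belongs to one variable, one effect and one significance level. Here the variable that was powered is not, as worded, among the declared primary outcomes, and two of those three have no power statement at all. A null result on duration or on 72-hour recovery could then be read as evidence of no benefit when the trial was never sized to find one.

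Three primary outcomes with one unadjusted threshold also leave open what a positive trial is. If the choice is made after the results are known, a single p<0.05 among the three could be reported as primary efficacy at an error rate above the stated 5%.

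**Working it through.** **Inputs from the protocol.** Three primary outcomes; 25% reduction in 48-hour stool output; alpha 5%; power 90%; dropout 10%; 46 per group, allocated 1:1; threshold p<0.05. Control mean, SD and sidedness are not given.

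**1. The plan's own figure.** The 46 cannot be reproduced without an SD, so it is solved backwards.
- Evaluable per arm: 46 × 0.9 = 41.4, so about 41 to 42.
- Standardised effect with 90% power, two-sided: d = √[2(1.960 + 1.282)² / 41.4] = 0.71.
- Implied SD/mean = 0.25 / 0.71 = 0.35. A one-sided test would imply about 0.39.

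So 46 is attainable, but only for 48-hour output and only if the SD is near 35% of the control mean. At 41 per arm, an assumed SD/mean of 0.5 gives about 62% power, and 0.8 gives about 29%.

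**2. Error rate if any one primary suffices.** Independent tests: 1 − 0.95³ = 14.3%. Simulation of three equicorrelated two-sided z-tests, 1,000,000 draws:

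| Correlation | Family-wise error |
|---|---|
| 0 | 14.3% |
| 0.3 | 13.6% |
| 0.5 | 12.5% |
| 0.7 | 10.9% |
| 0.9 | 8.4% |

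**3. If all three must succeed.** The error stays at or below 5%. Joint power is 0.9³ = 72.9% if each outcome had 90% and they were independent. Positive correlation raises it, but it can never exceed the power of the weakest of the three.

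**4. Power for the two outcomes without a power statement.** These use 41 evaluable per arm and a two-sided 5% level. The effects are illustrative assumptions and do not come from the protocol.
- 72-hour recovery, 50% versus 70%: [0.20 − 1.96√(2 × 0.6 × 0.4/41)] / √[(0.25 + 0.21)/41] = −0.11, so power is about 45%. For 50% versus 75% it is 65%. About 50% versus 83% is needed for 90%.
- Duration by log-rank, recovery-rate ratio 1.5: √(events/4) × ln 1.5 − 1.96. With 82 events this is −0.12 (45% power); with 78 events it is −0.17 (43%). A ratio of about 2.05 is needed for 90% with 82 events.

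**5. Cost of splitting alpha.** At 0.05/3 = 0.0167 the critical value is 2.394. Power for stool output at the implied effect is Φ(3.242 − 2.394) = Φ(0.848) = 80%. Restoring 90% needs 53 to 54 evaluable per arm, which is 59 to 60 per arm with 10% dropout.

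**The case against.** The strongest reply is that 48-hour output is not foreign to the outcome list. Stool is weighed every six hours, so the 48-hour total is the sum of eight weighings, or of the first two days of daily output. Stool output is also one of the two efficacy objectives. This stands. A reader might infer that the trial was powered on something unrelated to its primary outcomes, and the documents do not support that. What remains is that the listed outcome has no window, so the 90% carries over to it only if daily output is read as a 48-hour total. Nothing carries over to the other two.

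Second, multiplicity rules are commonly left to a statistical analysis plan, and the p<0.05 sentence is attached to the log-rank clause. That is fair for the details of adjustment. It does not reach the mismatch between primary outcomes and sample-size variable, because both are fixed in this protocol.

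Third, the protocol nowhere says that one success is enough. A reader might infer a 14.3% error rate as fact. That figure needs both an any-one rule and independence, and independence is implausible because 72-hour recovery is close to a dichotomy of duration.

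Two further inferences should be avoided. Duration is not left open to several competing tests, since Statistical methods ties it to the log-rank test. And 72-hour recovery is not a stated objective.

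**Conclusion.** The point holds as a mismatch. The declared primary outcomes and the variable behind the sample size are different, and no success rule joins them. Under an any-one rule the 5% is not held: about 8% to 14% over correlations 0.9 to 0. Under an all-three rule the 5% is held but the 90% is not: about 73% under independence, if each outcome had 90%. Under neither rule do both stated figures describe the three-outcome analysis.

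The 45% and 43% to 45% powers for the other two outcomes rest on assumed effects and show scale only. The calculations do not show that 46 per group is wrong for 48-hour stool output; they show that it cannot be checked without the missing mean, SD and sidedness. The mismatch should be corrected before the trial's results are analysed.

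**What to change.** In the Project Summary outcome list, the Output section and the sample-size section, name one primary outcome with a defined window that matches the sample-size basis: stool output over 0 to 48 hours from randomization, already obtainable from the six-hourly weights. Make duration, 72-hour recovery and any day-by-day output secondary, in a prespecified order. State that the 90% power applies to the primary outcome only. Give the control mean, SD and sidedness from the source trial. The implied SD/mean of about 0.35 (two-sided) is a check on those figures and must not be entered as if it were one of them.

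If the sponsor keeps three primaries, state whether one or all must succeed. If any one suffices, use Holm, restate the power for stool output as about 80% (its value at alpha 0.0167), and give the detectable differences for the other two.

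Either route is a change of wording and needs no extra children, provided the lower power is accepted in the second. Keeping 90% for stool output at 0.0167 would take 59 to 60 per arm instead of 46, which is 26 to 28 more children in all. The price of the first route is that duration and 72-hour recovery lose primary status; the price of the second is a lower stated power.

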## Definitions

**Abdominal distension** occurs when substances, such as air (gas) or fluid, accumulate in the abdomen causing its outward expansion beyond the normal girth of the stomach and waist. It will be evaluated by regular measurement of abdominal girth. No set parameters for abdominal distension. To measure the abdominal girth before the IP and repeat measurement daily. If there is change that is increase in diameter of girth measurement, then we will define distension. Recurrent abdominal pain or discomfort at least 3 days/month in the last 3 months. [28, 29]

**Abdominal pain:** Abdominal pain is felt in the part of the trunk below the ribs and above the pelvis. Abdominal pain comes from organs within the abdomen or organs adjacent to the abdomen. It will be measured by asking mother's perception whether the child had the history of cry, irritability which was associated with abdominal pain. [28]

**Rumbling:** A stomach rumble, also known as a bowel sound or peristaltic sound, is a rumbling, growling or gurgling noise produced by movement of the contents of the gastro-intestinal tract as they are propelled through the small intestine by a series of muscle contractions called peristalsis. It will be measured both by taking history from the parents and by abdominal auscultation.

**Bloating:** Bloating is the presence of abnormal general swelling, or increased in diameter of the abdominal area. Recurrent feeling of bloating or visible distension at least 3 days/month in the last 3 months [28]. It will also be evaluated by regular measurement of abdominal girth.

Flatulence: "flatus expelled through the anus" or the "quality or state of being flatulent", which is defined in turn as "marked by or affected with gases generated in the intestine or stomach; likely to cause digestive flatulence". It will be measured by taking history from the parents.

Stool consistency: Appearance of the stool; such as formed, mucoid, or liquid. This will be measured by direct visualization by the parents as well treating physicians.

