### *Study design of exploratory study*

We will conduct the study in two phases – in phase I the safety and tolerability issues will be examined among healthy **and diarrheal** children ( $n=30+30=60$ ), and if Fibersol-2 is found to be safe and tolerable, we will approach the DSMB to seek permission to extend the study for phase II as the clinical trial only in diarrheal children. The evaluable clinical signs include abdominal pain, rumbling, bloating, flatulence, and stool consistency.

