### **Study duration:**

1. Pre-study observation: 7 days [During the pre-study observation period our study staff members will collect clinical information as well as associated co-morbidity from control group children to see whether they are eligible for enrolment].
  2. Main study period : 7 days
  3. Post-study observation: 7 days [Our research staff will visit households as well as hospital to collect 1-day recall data regarding health status; caregivers will be informed that the research staff will visit for consecutive 7 days]
- Total observation period 21 days

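### The bloating and distension definitions do not work in Phase I: any rise in girth over one baseline reading counts, and a three-month recurrence criterion is attached to a 21-day observation

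*Protocol*

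**What the plan says.** **Distension (Protocol, Definitions).** The entry first states "No set parameters for abdominal distension". It then sets a schedule, "To measure the abdominal girth before the IP and repeat measurement daily", and a rule, "If there is change that is increase in diameter of girth measurement, then we will define distension". No minimum change, time of day or relation to feeding is given. The entry closes with a sentence on a different symptom, "Recurrent abdominal pain or discomfort at least 3 days/month in the last 3 months", with no word joining it to the girth rule.

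**Bloating (same section).** It is described as abnormal swelling or a larger abdominal diameter, then by "Recurrent feeling of bloating or visible distension at least 3 days/month in the last 3 months", and is finally said to be evaluated by girth as well.

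**Time available (Study duration).** "Main study period : 7 days", with 7 days before and 7 days after: "Total observation period 21 days".

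**Use of the signs (Study design of exploratory study).** Five signs are listed: abdominal pain, rumbling, bloating, flatulence and stool consistency. Bloating is on the list; distension is not named separately. The step to the trial is conditional: "if Fibersol-2 is found to be safe and tolerable, we will approach the DSMB to seek permission to extend the study for phase II". The background section adds that Phase I compares two doses and that the suitable one goes into the randomised trial. Under Methods for exploratory study, each dose has 15 healthy and 15 diarrhoeal children, and there is no placebo arm.

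**The concern.** A tolerability sign needs a definition that can be met when the product causes the problem and is seldom met when it does not. The two elements here fail in opposite directions.

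- The three-month criterion is worded as for a chronic disorder. It can describe a child's history, but an effect of one week of product cannot meet it during the study.
- The girth rule counts any increase over one reading. Tape error, meals and time of day will produce such increases in children whose abdomen has not changed.

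The text does not say whether a case needs both elements or either one. Two staff members could follow it faithfully and classify the same child differently. At stake is the evidence on bloating, which helps decide whether Phase II is proposed and at which dose.

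**Working it through.** **1. The plan's own figure.** 7 + 7 + 7 = 21 days of observation, as stated.

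**2. The three-month criterion.** Three months is about 3 × 28 = 84 to 3 × 31 = 93 days. A symptom that begins on product can be observed for at most 7 + 7 = 14 days. It cannot meet the criterion within Phase I.

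**3. The girth rule when nothing has changed.** Inputs: one baseline reading and daily repeats (Definitions), and 7 days of product (Study duration). Assumptions: a child is a case if any repeat exceeds baseline, and the readings vary only by noise and are exchangeable. The baseline is then the highest of the k + 1 readings with probability 1/(k + 1), so

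P(at least one of k repeats exceeds baseline) = k/(k + 1), whatever the SD.

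- k = 7 (product week): 7/8 = 87.5%; 15 × 0.875 = 13.1 of 15 children.
- k = 14 (if daily girths continue through the post-study week, assumed): 14/15 = 93.3%; 14 of 15 children.

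**4. Rounded readings.** Rounding creates ties, which are not increases. The protocol gives neither the reading unit nor the within-child SD, so both are assumed. Simulation with k = 7, 400,000 draws and true girth spread evenly over one reading unit:

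| Reading unit | SD 0.3 cm | SD 0.5 cm | SD 1.0 cm | SD 1.5 cm |
|---|---|---|---|---|
| 0.1 cm | 84% | 86% | 87% | 87% |
| 0.5 cm | 66% | 76% | 82% | 84% |
| 1 cm | 42% | 60% | 76% | 80% |

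**5. If girth falls as diarrhoea resolves.** With unrounded readings, SD 0.5 cm and k = 7, a true fall of 0.5 cm gives 61% and a fall of 1 cm gives 29% (illustrative).

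**6. Effect on the dose comparison for this sign.** Let f be the false-positive rate. Then observed rate = f + (1 − f) × true rate. Assume true rates of 10% and 50% with 15 children per dose and a two-sided 5% Fisher test:

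| f | Observed rates | Power |
|---|---|---|
| 0 | 10% v 50% | 54% |
| 0.50 | 55% v 75% | 10% |
| 0.75 | 77.5% v 87.5% | 4% |
| 0.875 | 88.75% v 93.75% | 1% |

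**7. How the elements combine.** If a case needs both the three-month criterion and the girth rise, no case can be caused by the product. If either suffices, most unchanged children are cases under most of the assumptions in step 4.

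**The case against.** The strongest reply is that the damage is local. A reader might infer from these definitions that Phase I can neither clear nor compare the doses. The protocol does not support that. Pain, rumbling, flatulence and stool consistency rest on parent report, auscultation or direct viewing, with no three-month window and no girth rule. Research Design and Methods also provides for close monitoring after each intake, with the physician called for any adverse event. The condition for Phase II is overall safety and tolerability, not a bloating threshold. This stands, and it limits the point to one listed sign.

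A reader might also infer that both signs require a three-month history. That is too strong. Under distension the three-month sentence concerns pain or discomfort and looks misplaced. Bloating is first described without a time window and is also judged by girth. A count of zero new cases therefore follows only if the elements are joined by 'and', which the text does not say.

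The 87.5% depends on counting a child as a case if ever above baseline; the section gives no rule for combining days. On any single day the noise rate is at most 50%. Coarse readings or falling girth lower the figure, so an event rate near 0% or near 90% whatever the product does is not established.

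Daily girth is also a continuous measurement, and Statistical methods already provides a t-test or nonparametric test for such data. The girths therefore keep information that the yes/no rule discards. Finally, even a clean definition gives only 54% power in step 6, so the small arms would limit the comparison anyway.

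None of this rescues the stated rules. They contradict each other, and following them faithfully would put the error into the data.

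**Conclusion.** The point holds for bloating and distension only. The three-month criterion cannot be met by an effect of the product within the 21-day observation; this needs no assumption. The girth rule has no allowance for measurement error and sits beside a statement that no parameters are set. It would label 87.5% of unchanged children over 7 daily readings, or 42% to 87% with rounded readings. Those figures assume an ever-above-baseline count, exchangeable readings, a within-child SD of 0.3 to 1.5 cm and a reading unit of 0.1 to 1 cm; they fall if girth declines with recovery.

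Without a placebo arm, Phase I cannot show this background rate. The yes/no result for one of its five signs would therefore say little about tolerability or about the difference between doses. Phase I as a whole is not invalidated. This is not a detail left to the statistical analysis plan, because the protocol itself fixes these definitions.

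**What to change.** 1. Delete the three-month wording from the distension and bloating definitions.
2. Define an on-study event as new, or worse than the child's own pre-product status, within the observation period, and state how symptom report and girth combine.
3. Count girth only when it exceeds baseline by a pre-set margin beyond measurement error. Set the margin from duplicate baseline readings.
4. Measure girth at the same time of day, before feeding. Duplicate readings capture tape error only, so timing has to be standardised to control the rest.
5. Compare daily girth change between doses as a continuous variable, with the methods already named in Statistical methods.

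The cost is protocol and case-form wording and one repeat tape reading at baseline. The downside is that very small rises are not counted. Daily girths in the pre-study week would help set the margin in healthy children, but Study duration does not plan them, so they are an optional addition. Requiring a rise on two consecutive days is a matter of preference and is not needed for the repair.
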